## 5.2. medication groups

All patients will be given medication.

## 5.3. procedures and timelines over time for interventions such as medication, surgery, and laboratory tests

The "study period" for each research subject will be from the date of obtaining consent to the date of completion of the outcome study in this study (Day365±21).

[figure not shown]

\*If there are MRI images that meet the criteria within 3 months prior to registration, they should be used.

### 5.3.1 Medication site, surgical site, examination site, etc.

(doses of) oral administration

### 5.3.2 Timing and duration of interventions such as medication, surgery, tests, etc.

After consent is obtained, the study drug "Ketsuyu Kaju-to" will be taken internally for 6 months.

### 5.3.3 Dosage, frequency, etc.

The dosage is adjusted according to the body weight of the research subject. 0.6 g/min per kg of body weight per day of the test drug "Ketsuyu Kaju-to" is orally administered before meals. The dosage may be adjusted according to the increase or decrease of body weight. The maximum dosage is 7.5 g/day. The duration of treatment is 6 months.

### 5.3.4 Protocol treatment

Treatment (dosage, administration, and duration of administration)

All patients will be treated with the study drug (Kesuyu Kadzhu-to).

The dosage is adjusted according to the body weight of the research subject. 0.6 g/min per kg of body weight per day of the test drug "Tsumura Ketsuyu Kadzhu-to Extract" is orally administered before meals. The dosage may be adjusted according to the increase or decrease in body weight. The maximum dosage is 7.5 g/day.

The administration period will be 6 months after the start of the study treatment. Dosing should be initiated immediately after enrollment, and thereafter should be administered three times a day in conjunction with breakfast, lunch, and dinner (before and after meal times).

### 5.3.5 Dose and Schedule Change Criteria

Postponement: not administering at the prescribed date and time, but delaying it.

Postponements may be taken after a meal or at a later time if the dose is not taken at the predetermined time due to forgetting to take it or for other reasons.

Discontinuation: permanent and continuous withdrawal of the entire treatment or a specific drug.

---

It is assumed that the drug will not be restarted.

Keep a record of the patient's medication intake and monitor the patient's medication status. If adherence is poor and the patient is unable to take the medication, discontinue the medication. In such a case, continue to monitor the patient.

#### **5.4 Adjunctive and Supportive Therapy**

Sclerotherapy, surgical resection, and concomitant use of mTOR inhibitors such as sirolimus and laparolimus are prohibited.

#### **5.5. post-treatment**

After discontinuation of protocol treatment or completion of protocol treatment, post-treatment is not restricted.

#### **5.6. discontinuation of protocol treatment**

The investigator or subinvestigator will discontinue the study drug if the investigator or subinvestigator determines that continuation of protocol treatment is not feasible for any of the following reasons. The date, reason, and progress of discontinuation will be documented in the medical record and the case report form (CRF), and necessary tests will be performed at the time of discontinuation or dropout to evaluate efficacy and safety.

If the drug is discontinued due to the occurrence of an adverse event, the patient should be followed up as much as possible until the current status is restored.

(1) When a research subject or a surrogate withdraws from participation in clinical research or withdraws his/her consent.

(2) When it is found that eligibility is not satisfied after registration

(iii) When the underlying disease is completely cured and there is no longer a need for continued administration

(iv) When it is determined that continued administration of the test drug is not desirable due to worsening of the underlying disease

(5) When it is difficult to continue the clinical research due to exacerbation of complications

(6) When it is difficult to continue the clinical research due to adverse events

(vii) In case of significant non-adherence (when it is determined that less than 70% of the total scheduled doses will be taken or more than 120% of the total scheduled doses will be taken)

(viii) If the research subject does not come to the hospital due to relocation, etc.

(ix) When the entire clinical research is discontinued

(10) When the principal investigator determines that it is appropriate to discontinue the clinical research for other reasons

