## 6.2. schedule for observation, inspection and reporting

### Observation, Inspection and Reporting Schedule

| (data) item                          |                 | Consent and screening                          | protocol treatment        | outcome study | time of discontinuance     |
|--------------------------------------|-----------------|------------------------------------------------|---------------------------|---------------|----------------------------|
| time                                 |                 | before the start of the test                   | Day 0 Day28 Day 84 Day168 | Day365        | Date of Decision to Cancel |
| Obtaining Consent                    |                 | ○                                              |                           |               |                            |
| Confirmation of medication adherence |                 |                                                | ○ ○ ○                     |               |                            |
| Background check                     |                 | ○                                              |                           |               |                            |
| test drug administration             |                 |                                                | ←→                        |               |                            |
| Observation of adverse events        |                 | ○                                              | ←→                        |               |                            |
| clinical examination                 | hematology      |                                                | ○ ○ ○ ○                   | △             | ○
○                     |
|                                      | blood chemistry |                                                | ○ ○ ○ ○                   |               |                            |
| MRI                                  |                 | ○note
(supplementary information)
symbol | ○                         | △             | ○                          |
| EO-5D-5L                             |                 |                                                | ○ ○                       |               |                            |

△Implementation: Implemented when possible

\*If there are MRI images that meet the criteria within 3 months prior to registration, they should be used.

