## 9.2. secondary endpoints

1. percentage decrease of more than 50% of volume

2. lesion reduction rate

3. 10% improvement in quality of life associated with treatment

4. safety of administration of koshuizhuyuu

5. adherence to the administration of Koshuizhuyuu (percentage of patients who were able to take

---

at least 70% of their medications)

Rationale: 3) Even if there is no marked change in size, QOL and symptom improvement has been reported, so it was set as a secondary endpoint; 4) Pseudohyperaldosteronism is known to be a major side effect of Eppikajutsuto, but its occurrence in children is not well reported.

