## **10. statistical considerations**

### **10.1 Basis for Setting Target Number of Cases**

In our retrospective case series study, the response rate (20% volume reduction at 6 months) to treatment with Eppikajutsuto in LM patients was 83% (in submission). Conservatively taking into account the overestimation tendency of the retrospective study design of prior reports, we expect a response rate of at least 50% with this treatment in the study's patient population. In the same study, none of the patients had a response to no treatment, and both patients had an increasing trend. Considering the exploratory nature of this study, the first prospective clinical trial, the number of patients will be designed based on accuracy. The lower limit of the two-sided 90% confidence interval (corresponding to a one-sided significance level of 5%) is 29.1% (the upper limit is 70.8%) if 9 patients respond (response rate of 50%) in the 18 patients in the analysis.

Considering that the main purpose of this exploratory study is to collect information that can be used for the next phase of the study, we believe that 18 cases is an appropriate number of cases. Since the number of patients seen annually at each site is approximately 5 cases each, it is possible to enroll the target number of cases in 3 years.

Based on the above considerations, the target number of cases was set at 20 to ensure accuracy in case a few cases were excluded from the analysis.

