## **10.3 Analysis Items and Methods**

### **10.3.1. primary endpoint primary analysis method**

For the primary endpoint of the study, the response rate will be based on whether or not patients achieve a reduction in lymphatic malformation volume by volumetry of at least 20% from the pre-treatment level at 6 months of treatment with the drug. An exact method based on a binomial distribution will be used for interval estimation. The significance level for the main analysis is 5% one-sided, and the corresponding two-sided 90% confidence interval is calculated.

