### 10.3.6 Handling of Missing Data, etc.

Missing values are not compensated for, and unless otherwise noted as the analysis method, the analysis is performed without using the completion method.

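### No EQ-5D-5L is scheduled at discontinuation, so the 10% quality-of-life improvement rate will rest mainly on children who stay on treatment

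*Protocol*

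**What the plan says.** Section 5.6 lists ten reasons for stopping the study drug. It requires the date, reason and progress of discontinuation to be documented in the medical record and the case report form, and adds that "necessary tests will be performed at the time of discontinuation or dropout to evaluate efficacy and safety". It does not list those tests.

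The list has to come from the section 6.2 schedule, whose last column is headed "Date of Decision to Cancel". As extracted, that column has marks for blood tests and MRI. The EQ-5D-5L row has two marks, both in the protocol-treatment block. The row "Confirmation of medication adherence" has three, also in that block. Section 6.1 names both items without a time point.

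Section 9.2 makes a 10% quality-of-life improvement a secondary endpoint, and section 10.3.3 item 3 turns it into the percentage of children reaching it. A further secondary endpoint is the percentage of children able to take "at least 70% of their medications". Section 10.2 analyses secondary endpoints primarily in the full analysis set (FAS), and stopping treatment is not a ground for exclusion from it. Section 10.3.6 states: "Missing values are not compensated for".

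**The concern.** A child stopped at about Day 60 for worsening or an adverse event will have a baseline EQ-5D-5L and no later one, while an MRI is scheduled for the same child at the same moment. The child remains in the FAS but contributes nothing to the quality-of-life rate.

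The MRI cannot stand in for the form. Section 9.2 justifies this endpoint by reports that quality of life and symptoms improve even when size changes little. A form given later would not repair the gap either: section 5.5 leaves treatment after discontinuation unrestricted, so a score at Day 168 could reflect surgery, sclerotherapy or an mTOR inhibitor.

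What is at stake is a named secondary endpoint in a study meant to inform the next phase. If the children who stop are those who gain least, the reported rate describes completers and reads better than the experience of all treated children.

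**Working it through.** **Does the schedule leave room for a discontinuation form?** The table is damaged in extraction, so it is safer to count marks than to trust their positions.

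- EQ-5D-5L: two marks. A before-and-after improvement needs one at baseline and one at the end of treatment. None is left over.
- Adherence: three marks, which match Day 28, Day 84 and Day 168. None is left over.
- MRI: four marks, which match pre-treatment, end of treatment, the optional Day 365 scan and discontinuation.

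The counts support the reading that MRI is scheduled at discontinuation and EQ-5D-5L is not.

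**The plan's own precision figure.** Section 10.1 gives a two-sided 90% interval of 29.1% to 70.8% for 9 responders in 18. The exact binomial (Clopper-Pearson) interval is 29.12% to 70.88%. The figure reproduces, with the upper limit truncated. It shows the scale of the random error against which the missing-data effect should be judged.

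**Effect of unmeasured children on the quality-of-life rate.** Inputs:

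- N = 20, the target in section 10.1, assumed here to be the FAS.
- d = children without a second EQ-5D-5L. The protocol gives no rate, so d = 2, 4 and 6 are assumptions. Section 10.1 allows for 2 exclusions (20 enrolled, 18 analysed), but these are not discontinuations.
- x = improvers among the N − d measured, set so that the measured rate is 50% (an assumption).

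The measured rate is x/(N − d). The full-set rate lies between x/N, if no unmeasured child improved, and (x + d)/N, if all did.

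| d | Measured rate | None improved | All improved |
|---|---|---|---|
| 2 | 9/18 = 50% | 9/20 = 45% | 11/20 = 55% |
| 4 | 8/16 = 50% | 8/20 = 40% | 12/20 = 60% |
| 6 | 7/14 = 50% | 7/20 = 35% | 13/20 = 65% |

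**Direction.** Write p_s for the improvement rate in measured children and p_d for the rate in unmeasured children. Then

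measured rate − full-set rate = (d/N) × (p_s − p_d).

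With d = 4 and p_s = 50%, the overstatement is 0.2 × (50 − 0) = 10 points if p_d = 0%, 0.2 × (50 − 25) = 5 points if p_d = 25%, and nil if p_d = 50%. If p_d = 100% the rate is understated by 10 points. Inflation therefore requires unmeasured children to improve less often than measured ones.

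**Adherence.** This endpoint does not depend on the visit marks alone. Section 5.3.5 requires a running record of intake, section 5.6 requires the stopping reason to be documented, and section 11.1 puts drug administration in the case report form. Section 5.6(vii) also uses the endpoint's own 70% cut-off, so a child stopped for intake below 70% is identifiable as an adherence failure. What stays open is the denominator. A child who takes every dose and stops at Day 60 for an adverse event has 60/60 = 100% of doses scheduled up to stopping, but 60/168 = 36% of the full course. Section 9.2 does not say which applies.

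**The case against.** The strongest reply has four parts.

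1. The schedule is visibly damaged: day columns are merged and both discontinuation blood-test marks sit in the haematology row. The wording of section 5.6 does not exclude a questionnaire. This stands as a caution. The empty EQ-5D-5L cell is probable rather than certain, although the mark count points the same way.

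2. A reader might infer that the quality-of-life rate is inflated as a matter of fact. The documents do not support that. No discontinuation rate is given, and the reasons in section 5.6 include complete cure, relocation and closure of the study as well as worsening, complications, adverse events and non-adherence. Overstatement is the likelier direction, not an established one.

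3. A reader might also infer that adherence is measured mainly in children who stay on treatment, and so is inflated too. That fails. The intake record and the stopping reason exist for children who stop, including those who stop before Day 28. If they are used, no adherence result need be lost, and nothing in the protocol says to ignore them.

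4. How unmeasured children count is often left to a statistical analysis plan, and these are secondary endpoints in an exploratory single-arm study. Both are true and limit the weight of the point. But no analysis plan can recover a form that was never given, so the collection gap belongs to the protocol. A discontinuation form will also not reach children whose consent is withdrawn or who no longer attend.

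**Conclusion.** The point holds for quality of life. On the most natural reading of section 6.2, a child who stops before the end-of-treatment form has no quality-of-life outcome but stays in the FAS, and nothing compensates for the gap. The improvement rate then rests mainly on children who stay on treatment. It is likely, but not certain, to overstate benefit. With 20 in the FAS and 50% among those measured, the uncertainty is 5 points either way for 2 unmeasured children and 10 points either way for 4. These figures rest on assumed dropout counts and an assumed rate, and are smaller than the random error at this sample size.

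For adherence, only two details need settling: a closing intake count at stopping, and the denominator of the 70%. The primary endpoint is untouched, because an MRI is scheduled at discontinuation. This is a cheap improvement, not a flaw that undermines the study.

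**What to change.** - **Section 6.2:** mark EQ-5D-5L in the discontinuation column, using the same self-complete or proxy version as at baseline, taken with the discontinuation MRI. Name it among the tests promised in section 5.6.
- **Section 10.3.3 item 3:** report the improvement rate on the FAS with the number of children unmeasured. Add a sensitivity analysis that counts children without a score as not improved if they stopped for worsening, complications, adverse events or non-adherence. Show cure, relocation and study closure separately. Scoring every early stopper as not improved is debatable, since it would make failures of cured and relocated children, so it should not be the main analysis.
- **Adherence (section 6.2 and section 10.3.3 item 5):** close the intake count at discontinuation, and state whether the 70% refers to the full 6 months or to doses scheduled up to stopping.

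The cost is one short questionnaire and one count at an assessment that already includes MRI and blood tests, plus a few sentences of analysis text. The reported quality-of-life percentage may come out lower. No treatment or stopping rule changes.

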#### **5.7 Control of Investigational Drugs, etc.**

The study drug custodian will manage the provided study drug, residual study drug, and disbursement of the study drug. The test drug(s) shall be used only for this study and shall not be used for any other purpose.

To maintain the quality of the test drug, it should be stored in a cool place out of direct sunlight and away from moisture as much as possible.

## **6. observation, examination, and reporting items and schedule**

### **6.1. observation and examination items and treatment information to be reported**

- before the start of the test

Research subject information: identification code, gender, date of birth, height, weight, complications, pre-existing medical conditions, current medical history, previous treatment, and allergies.

Blood tests: blood count, platelets, peripheral hemogram

Blood biochemical tests: BUN, Cr, T-Bil, AST-GOT, ALT-GPT, LDH,  $\gamma$ GTP, Na, K, Cl, T-Chol,

CRP

Diagnostic Imaging (MRI)

- Day28 (Tolerance: Day28 $\pm$ 3), Day84 (Tolerance: Day84 $\pm$ 7)

Blood tests: blood count, platelets, peripheral hemogram

Blood biochemical tests: BUN, Cr, T-Bil, AST-GOT, ALT-GPT, LDH,  $\gamma$ GTP, Na, K, Cl, T-Chol,

CRP

- Day 168 (Tolerance: Day 168  $\pm$  14)

Blood tests: blood count, platelets, peripheral hemogram

Blood biochemical tests: BUN, Cr, T-Bil, AST-GOT, ALT-GPT, LDH,  $\gamma$ GTP, Na, K, Cl, T-Chol,

CRP

Diagnostic Imaging (MRI)

- Outcome study (Day365 $\pm$ 21)

The course of symptoms will be followed, including the frequency of requests for continued use of Eppikajutsuto after completion of protocol treatment and a subsequent survey of medical records.

- Confirmation of medication adherence

- QOL questionnaire survey by EQ-5D-5L Japanese version for Japan.

## 6.2. schedule for observation, inspection and reporting

### Observation, Inspection and Reporting Schedule

| (data) item                          |                 | Consent and screening                          | protocol treatment        | outcome study | time of discontinuance     |
|--------------------------------------|-----------------|------------------------------------------------|---------------------------|---------------|----------------------------|
| time                                 |                 | before the start of the test                   | Day 0 Day28 Day 84 Day168 | Day365        | Date of Decision to Cancel |
| Obtaining Consent                    |                 | ○                                              |                           |               |                            |
| Confirmation of medication adherence |                 |                                                | ○ ○ ○                     |               |                            |
| Background check                     |                 | ○                                              |                           |               |                            |
| test drug administration             |                 |                                                | ←→                        |               |                            |
| Observation of adverse events        |                 | ○                                              | ←→                        |               |                            |
| clinical examination                 | hematology      |                                                | ○ ○ ○ ○                   | △             | ○
○                     |
|                                      | blood chemistry |                                                | ○ ○ ○ ○                   |               |                            |
| MRI                                  |                 | ○note
(supplementary information)
symbol | ○                         | △             | ○                          |
| EO-5D-5L                             |                 |                                                | ○ ○                       |               |                            |

△Implementation: Implemented when possible

\*If there are MRI images that meet the criteria within 3 months prior to registration, they should be used.

### 6.3. preservation of samples, etc. and use of samples, etc. by other institutions, etc.

MRI imaging data, medical data, and blood test data will be provided to the investigators for before and after comparison of the effects of the study drug. The principal investigator will instruct the subinvestigators to properly store the samples in accordance with the established storage methods, and will take necessary measures to prevent leakage, mixing, theft, or loss of the samples. The amount of blood collected should be between 3 ml and 10 ml depending on the method of blood collection, and the collected serum or plasma should be stored frozen at each medical institution until March 31, 2028 after the completion of the clinical research. When disposing of the samples, they will be anonymized and personal information will be carefully handled.

Samples and information of research subjects obtained in such clinical research may be used for future research that is not identified at the time consent is obtained. In such a case, the research will

be conducted only after the implementation of the research based on the samples obtained in the relevant clinical research is reviewed by an ethical review committee in accordance with the content of the research and is separately explained to the research subject and the surrogate consentor.

